### Study setting

This is a Dutch CRCT (Trial registration: Netherlands Trial Register: NL8518). The protocol of the study and data management plan have been uploaded to Open Science Framework (https://doi.org/10.17605/OSF.IO/KDUYS). The trial will be conducted in physical therapy practices in the Netherlands. Participating physical therapy practices will be the unit of randomisation (cluster). Working patients with MSDs visiting a physical therapy practice are the target group. The control group will receive regular physical therapy treatment. The intervention group will receive treatment from a physical therapist with more knowledge about work-related factors and more skills in terms of integrating work participation into the patients’ care.

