### Procedures

As soon as a physical therapy practice confirms participation in this study, they will receive an email from the principal investigator indicating to which group they have been allocated. All participating physical therapists will receive patient information about the study and materials needed for the inclusion of patients. Patients will be recruited and informed by the participating physical therapy practices. Consecutive patients will be asked if they are willing to participate in this study and will receive the information letter. Patients will be allowed to use all the time they need to consider their participation. As soon as a patient has decided to participate, the first consult will be planned. Patients will also receive an information letter and will be given the time they need to consider their participation. If patients do not want to participate in the study, they will receive regular physical therapy treatment and will not be enrolled in the study. If patients want to participate in the study, the physical therapist will assess them for eligibility during the intake and ask for written informed consent and their contact details. The physical therapist will then send the contact details to the investigators via a secured app (Siilo, Siilo Holding B.V., the Netherlands). An image of the informed consent form will also be sent to the investigators via a secured app. The original form will be sent by regular mail or will be collected by the investigators.

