### Outcome assessment and data collection

All outcome measures will be self-reported measures. Data will be collected using online questionnaires filled in by the participating patients at the start of the intervention (T0), four months after the start of the intervention (T1, short-term effects) and eight months after the start of the intervention (T2, long-term effects). All questionnaires will be developed using Qualtrics online survey software (Qualtrics®). Outcome measures will be collected from the patients. The schedule for enrolment, outcome measures and time points is summarised in Table 1. Physical therapists will be asked to fill in a questionnaire at the start of the intervention and after eight months.

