#### Secondary outcomes

**Limitations in general work-related activities** will be assessed using a single question about the limitations experienced during work in general due to the complaints (11-point scale) [38].

**General pain**. The general level of pain experienced by the patient in the previous week will be assessed using the 11-point numeric pain rating scale (NPRS).

**Quality of life** will be assessed using the 12-item Short-Form Health Survey (SF-12) [39].

**Presenteeism** will be assessed using the Dutch version of the 6-item Stanford Presenteeism Scale (SPS-6) [40].

**Absenteeism** will be measured by asking the patient the number of days they had been out of work due to their complaints during the previous month.

**Estimated risk for future work disability** will be assessed using the Örebro Musculoskeletal Pain Screening Questionnaire (short form) [41].

**Work-related psychosocial risk factors** will be assessed using the blue flags questionnaire [42].

The degree to which health problems interfere with specific aspects of **job performance** and the **productivity impact** of these work limitations will be assessed using the Work Limitations Questionnaire [43].

**Work ability** will be assessed using the Work Ability Index-Single Item Scale (WAS), which is a responsive measure for work participation and highly predictive for future sickness absence [44].

The amount of **attention to work participation** given by the physical therapist, and the **level of satisfaction** of the patient with this attention will be measured using five-point Likert scales.

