### Sample size

The sample size was calculated based on the main outcome measures (11-item NPRS and 11-point PSFS), an expected effect size of 0.7 and a standard deviation of 1.8 [32, 45–47]. On the basis of two-sided testing, significance level of 0.05, power 0.8, accounting for the cluster design effect, assuming an ICC coefficient of 0.05, and 15 clusters per intervention arm, an effective sample size would require 10 patients per cluster (i.e. per physical therapy practice). With respect to the effect of cluster size variation, we added 10% additional clusters (in total 17 clusters per arm) [48]. Allowing for a 25% loss to follow-up, we would need to recruit 13 participants (i.e. patients) per cluster [49]. In total, we need to include 221 patients in each arm (442 in total).

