### Data analyses

Analysis of the two groups will be conducted blinded to the treatment allocation and the data will be analysed according to the intention-to-treat principle. Baseline characteristics of the participants will be presented in means and standard deviations (symmetrically distributed continuous variables), median interquartile ranges (other continuous variables), and counts and percentages (categorical variables), and will be checked for baseline differences between the two groups.

All outcome measurements will be continuous variables and will be presented as means and standard deviations. Normality of the data will be checked and verified using histograms, normal probability plots and Shapiro-Wilk tests. Between-group differences for all outcomes will be analysed using linear regression. If data appears to be not normally distributed, Mann-Whitney U tests or log transformation will be performed.

Each outcome variable will be analysed independently at T1 and at T2 [50] as a dependent variable using the study group as an independent variable, adjusted for the baseline measurement of each outcome measure. Adjustment for confounding will only be applied if the regression coefficient of the intervention variable changes by more than 10% when the potential confounding variable is added to the model. If missing data for an outcome is > 5%, multiple imputation will be conducted. Results will be considered significant if p < 0.05. All analyses will be performed using IBM SPSS Statistics 26 (IBM Corporation).

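### The blanket baseline-adjustment rule covers two secondary outcomes (attention to work and satisfaction with it) that have no true pre-treatment value, and may remove part of the arm difference if they are rated at T0

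*Protocol article*

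**What the plan says.** **The model.** The Data analyses section sets one approach for everything: "Between-group differences for all outcomes will be analysed using linear regression". Each outcome is taken at T1 and at T2 separately "as a dependent variable using the study group as an independent variable, adjusted for the baseline measurement of each outcome measure". No outcome is exempted. If the data are not normal, the section allows a Mann-Whitney U test or a log transformation.

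**The two outcomes.** The list of secondary outcomes ends with how much attention the therapist paid to work participation and how satisfied the patient was with it. The level of satisfaction "of the patient with this attention will be measured using five-point Likert scales", as is the attention itself.

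**The timing.** The Trial design section says that outcomes are assessed at baseline and at four and eight months. The Outcome assessment and data collection section describes online questionnaires "filled in by the participating patients at the start of the intervention (T0" and again at T1 and T2. It leaves the item-by-item schedule to Table 1, which is not shown.

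**The order of events.** Under Procedures, as soon as a practice confirms participation, "they will receive an email from the principal investigator indicating to which group they have been allocated". For patients who want to take part, "the physical therapist will assess them for eligibility during the intake and ask for written informed consent and their contact details". Only then do the contact details go to the investigators.

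**The concern.** A baseline covariate helps when it is measured before treatment can act on it. These two items rate what the therapist does in this episode of care. Before the therapist has seen the patient there is nothing to rate. A rating taken after the intake would describe a contact that the allocation may already have shaped. The Study setting section says that patients in the intervention arm are treated by a therapist with "more knowledge about work-related factors and more skills in terms of integrating work participation into the patients’ care", so attention to work is exactly what the intervention is meant to change.

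Adjusting a follow-up rating for an earlier rating that already carries some of the arm effect removes part of the contrast of interest. That contrast is a direct patient-reported indication, comparable between arms, of whether the intervention reached the patient. If it is understated, a null result on the primary outcomes becomes harder to interpret: the intervention may have been delivered without benefit, or not delivered.

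**Working it through.** **Figures in the plan.** No stated figure depends on this point. As a check that it leaves the sample size alone, the published calculation was reproduced from "an expected effect size of 0.7 and a standard deviation of 1.8" with two-sided 0.05, power 0.8, ICC 0.05 and 10 patients per cluster:

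- Individually randomised: 2 × (1.8 × (1.960 + 0.842) / 0.7)² = 103.8 per arm.
- Design effect: 1 + (10 − 1) × 0.05 = 1.45, so 103.8 × 1.45 = 150.5, against 15 × 10 = 150.
- Clusters: 15 × 1.1 = 16.5, rounded to 17. Patients per cluster: 10 × 1.25 = 12.5, rounded to 13. Total: 17 × 13 = 221 per arm, as stated.

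The two items enter nowhere.

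**Two cases, because Table 1 is not shown.**

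*Case A: the items are not asked at T0.* The covariate named in the rule does not exist. The sensible reading is a model with study group alone, and no effect is lost.

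*Case B: the items are asked at T0.* The practice knows its arm once it has confirmed participation. Intake, eligibility check and consent come next, then the contact details go to the investigators. The online T0 questionnaire most likely follows. This order is put together from the Procedures and the Outcome assessment and data collection sections; neither states it outright.

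**Size in case B.** Let D1 be the true arm difference at the follow-up analysed, D0 the arm difference already present at T0, and r the within-arm correlation between the two ratings, with equal variances. The within-arm slope on the T0 rating is then r, and the group coefficient is

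adjusted difference = D1 − r × D0.

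With D0 = f × D1 this becomes (1 − r·f) × D1. The documents give neither r nor f; all values below are assumed.

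| r | f = 0 | f = 0.2 | f = 0.5 | f = 1 |
|---|---|---|---|---|
| 0.3 | 100% kept | 94% | 85% | 70% |
| 0.5 | 100% kept | 90% | 75% | 50% |
| 0.7 | 100% kept | 86% | 65% | 30% |

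Example: r = 0.5 and f = 0.5 give 1 − 0.25 = 0.75, so a quarter of the difference is lost.

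**Simulation check** (200,000 simulated patients, true difference 0.5 SD, least squares on group and T0 rating). Share of the true difference recovered:

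- r = 0.5, f = 1: 0.51 (formula 0.50)
- r = 0.5, f = 0.5: 0.75 (0.75)
- r = 0.7, f = 1: 0.30 (0.30)
- r = 0.5, f = 0: 1.00 (1.00)

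Without the T0 term, the group coefficient estimates the whole difference in every row.

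**The case against.** **The schedule is not visible.** Table 1 may list these items at T1 and T2 only. The rule would then be a loose sentence in a condensed article, applied wherever a baseline exists. This stands as a limit on the consequence: in that case nothing is lost. A reader might infer that the outcomes would be left without an analysis, but the group term can simply be fitted alone. The rule as written still names a covariate that these outcomes cannot properly have.

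**The bias needs an early arm difference.** Attention to work should build up over a course of care, and at T0 there has been at most about one contact. This also stands. A reader might take 30% to 70% as the expected loss, but that range needs the full arm difference to be present at T0. At f = 0.2 and r of 0.3 to 0.5 the loss is 6% to 10%.

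**The plan has a fallback without a covariate.** Five-point items may fail the normality check, and a Mann-Whitney test uses no baseline. But that route is conditional, and log transformation is offered as its alternative, so the rule is not displaced.

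**There are other signs of delivery.** A reader might infer that attention to work is the only patient-level evidence, in both arms, that the intervention arrived. The documents do not support that. The section on other measures also collects referrals to occupational health professionals, without limiting them to one arm, and therapist knowledge, attitude and self-efficacy in both arms. The process interviews add to this, in the intervention arm only. None of these measures the attention that the patient received in the consultation, but a null primary result would not be read from this item alone.

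**A T0 question could be about earlier care or expectations.** That would avoid the bias, but it would not be a baseline of the same outcome.

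**Conclusion.** The point holds in a limited form. The adjustment rule is universal, and it is unsuitable for two secondary outcomes that rate care given during the trial. If these are rated at T0 after the intake, adjustment removes part of the arm difference: nothing at f = 0, 15% to 35% at f = 0.5 and 30% to 70% at f = 1, for r of 0.3 to 0.7. These figures rest on assumed r and f, equal variances at the two times, and an inferred order of intake before T0. If the items are not asked at T0, the stated covariate is absent and no effect is lost.

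A stronger conclusion, that the plan adjusts away the effect, is not supported: complete removal needs r·f = 1. The primary outcomes, which can have a T0 value, and the sample size of 221 per arm are unaffected. The correction is worth making because it costs almost nothing and protects a direct patient-reported comparison of delivery.

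**What to change.** Add one sentence to the Data analyses section: attention to work participation and satisfaction with it are exempt from baseline adjustment, and the arms are compared at T1 and at T2 on study group without any T0 value of these items. Covariates that are truly pre-randomisation may still be used.

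Keep all patients of the randomised practices in both comparisons. It may be tempting to ask these items at T2 only of patients treated since T1, but this should not be done. The Background section expects the intervention to lead to fewer sessions and fewer recurrences, so being treated after T1 may itself depend on arm. Selecting on it would break the randomised comparison and the intention-to-treat principle that the plan sets. Patients who have finished treatment can still rate the care they received.

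Cost: one sentence, with no new data and no change to the sample size.

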#### Descriptive data

Characteristics of the patients will be collected at baseline in the first questionnaire. Patient characteristics include age, gender, education, family status, area of complaints, duration of complaints, profession and work/workplace, and hours of employment.

Characteristics of the physical therapists will be collected at baseline with the first questionnaire. Physical therapist characteristics include age, gender, education, area of specialisation and years of experience as a physical therapist.

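### Covariates beyond the baseline outcome are chosen by how far they move the treatment estimate, so the primary model depends on the result and loses some precision

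*Protocol article*

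**What the plan says.** All of this is in the protocol article, mostly under Data analyses.

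- **Outcomes and times.** "Each outcome variable will be analysed independently at T1 and at T2", by linear regression on study group.
- **Fixed covariate.** Every model is "adjusted for the baseline measurement of each outcome measure", so the baseline value of the outcome is always included.
- **Further covariates.** "Adjustment for confounding will only be applied if the regression coefficient of the intervention variable changes by more than 10" per cent "when the potential confounding variable is added to the model". The rule gives no absolute threshold.
- **Data available.** Under Descriptive data: "Patient characteristics include age, gender, education, family status, area of complaints, duration of complaints, profession and work/workplace, and hours of employment". These are not called confounders.
- **Planned effect.** Under Sample size: "an expected effect size of 0.7 and a standard deviation of 1.8".

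**The concern.** A change-in-estimate rule belongs to observational work, where a shift in the exposure coefficient is read as a sign of confounding. Here the practices are randomised. Part of any shift is chance imbalance, and the yardstick is the treatment estimate itself.

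Two things follow. First, whether a covariate enters depends on the size of the observed effect as well as on how prognostic or unbalanced the covariate is. A small estimate makes the threshold tiny, and a large one makes it hard to reach. Second, the rule is applied analysis by analysis. Two primary outcomes at two follow-up times give four primary models, and each may carry a different covariate set. At stake are a primary model fixed before the data are seen, and the precision that prognostic covariates would give.

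**Working it through.** **Inputs from the protocol article (Sample size):** planned difference 0.7, SD 1.8, ICC 0.05, 10 analysed patients per cluster, 15 clusters per arm raised to 17, and 13 recruited per cluster.

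**Assumed, because the document does not give them:** number of candidate covariates, their independence, their correlation with the outcome, and a covariate ICC of 0.05.

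**1. The plan's own figure.** Two means: 2 × (1.96 + 0.84)² × 1.8² / 0.7² ≈ 104 per arm. Design effect: 1 + 9 × 0.05 = 1.45. Then 104 × 1.45 = 150.8, about 15 clusters of 10. Next, 15 × 1.1 = 16.5, taken as 17, and 17 × 13 = 221 per arm. The stated figure is reproduced, and the present point does not change it.

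**2. The threshold.** Threshold = 0.10 × |estimate|.

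| Estimate | Shift needed to enter |
|---|---|
| 0.70 | 0.070 |
| 0.35 | 0.035 |
| 0.10 | 0.010 |

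With 170 analysed per arm, the standard error of the difference before baseline adjustment is about √(2 × 1.8² × 1.45 / 170) = 0.235. An estimate near 0.1 is thus well within the noise, and so is a shift of 0.01.

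**3. How far one covariate moves the estimate.** Adding a covariate shifts the treatment coefficient by (covariate's coefficient) × (between-arm difference in the covariate). For a standardised covariate, the chance difference has SD √(2 × 1.45 / 170) = 0.131. With correlation 0.2, the coefficient is 0.2 × 1.8 = 0.36, so the shift has SD 0.36 × 0.131 = 0.047. Taking the shift as normal:

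- estimate 0.7: P(|Z| > 0.070/0.047) ≈ 14%
- estimate 0.35: P(|Z| > 0.035/0.047) ≈ 46%
- estimate 0.1: P(|Z| > 0.010/0.047) ≈ 83%

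The same covariate goes from seldom entering to usually entering only because the estimate is smaller. This approximation ignores error in the covariate's own coefficient and variation in the estimate. The simulations below include both.

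**4. One candidate, simulated** (17 clusters of 10 per arm, ICC 0.05, baseline outcome always in the model). Chance that the covariate enters:

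| Correlation with outcome | True effect 0.7 | 0.35 | 0 |
|---|---|---|---|
| 0.1 | 4% | 25% | 46% |
| 0.2 | 19% | 48% | 69% |
| 0.3 | 35% | 62% | 79% |

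A covariate unrelated to the outcome enters in about 1% of trials at 0.7, in 24% with no effect, and in 54% of the no-effect trials whose estimate is below 0.1 in size.

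**5. Several candidates.** With six independent candidates at standardised coefficients 0.1 to 0.2 and the same clustering, at least one enters in about 91% to 99% of trials with no effect and in 19% to 56% at 0.7. With eight candidates at correlations 0.1 and 0.2, the figures are 91% to 99% and 27% to 65%.

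**6. What it does to inference.** In the six-candidate clustered run, type I error under the rule was 0.043 to 0.047, coverage of the 95% interval 0.94 to 0.96, and bias about 0.01 points. Precision at a true effect of 0.7:

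| Coefficient | SD, rule | SD, fixed set | Variance ratio |
|---|---|---|---|
| 0.1 | 0.207 | 0.203 | (0.207/0.203)² = 1.04 |
| 0.2 | 0.188 | 0.171 | (0.188/0.171)² = 1.21 |

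With eight candidates at correlation 0.2 and cluster-robust standard errors, power at 0.7 was 0.94 with the fixed set, 0.90 under the rule, and 0.84 with no further covariates.

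**The case against.** The best defence is that the rule does little inferential harm. A reader might infer that choosing covariates on the treatment coefficient invalidates the p-value or the interval. The calculations do not support that: error rate and coverage stay near nominal, and the bias is trivial against the two-point minimal important difference the article uses. This part of the defence stands.

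Other points in the plan's favour:

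- **Blinded, mechanical analysis.** The data are to be analysed blind to allocation and the threshold is a fixed percentage. This limits steering towards a favoured arm. It does not hide the size of the coefficient, which is what the rule acts on.
- **Real imbalance is possible.** Practices know their arm before their therapists recruit, so patient differences may exceed chance and a concern about confounding is not misplaced. That argues for adjusting for named prognostic variables, whatever the estimate turns out to be.
- **The baseline check.** Baseline characteristics are to be presented "and will be checked for baseline differences between the two groups". A reader might take this as a second route to adjustment. The article places it with the descriptive summaries and links it to no model.
- **Unnamed candidates.** The article lists no candidates beside the rule, but a fuller protocol is said to be uploaded elsewhere and is not shown. Their absence here is no defect.
- **Sensitivity to assumptions.** The entry rates depend on how many candidates there are and how prognostic they are. The direction held in every setting tried, but the exact percentages should not be read as predictions.

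**Conclusion.** The concern holds in a limited form. As stated, the rule makes every covariate other than the baseline outcome conditional on the estimated effect, so the primary model is not fixed in advance and may vary across outcomes and times. Saying that adjustment is almost always triggered when there is no effect would be right only for at least one of several candidates. A single candidate with correlation 0.1 to 0.3 enters in 46% to 79% of such trials.

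The measurable cost is precision. At the planned effect, the variance of the estimate is about 4% higher than with a fixed set if the six candidates are weak (0.1), and about 21% higher if they are moderate (0.2). Both figures rest on assumed, independent candidates with ICC 0.05. The result is not an invalid test. The change is worth making because it is cheap and removes a dependence of the model on its own answer.

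**What to change.** Delete the 10% rule under Data analyses. In its place, state that every outcome at T1 and at T2 is adjusted for its baseline value plus a short fixed list of prognostic characteristics already collected at baseline, for example age, gender, duration of complaints and area of complaints, whatever their effect on the treatment coefficient. Report the model adjusted for the baseline outcome only as a sensitivity analysis.

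This takes about one sentence and no new data. The price is a few degrees of freedom out of about 340 analysed patients (2 × 17 × 10), plus the need to settle the list before the outcome data are examined. The sample size is unaffected.

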### Randomisation and blinding

The physical therapy practices of the participating physical therapists will be the unit of randomisation (cluster). Each practice will be randomly assigned to either the intervention or control arm on a 1:1 basis. The allocation sequence will be generated online (with a block size of six) [25] using http://randomization.com by the principal investigator. Participating practices will be randomised in the order that they confirm their participation in the study. The practices will be informed about the group allocation by the principal investigator. Based on the randomisation, physical therapists working in the randomised practices will be able to use all the ‘WORK TO BE DONE’ intervention components (intervention group) or will continue providing regular physical therapy to their patients (control group). Physical therapists and patients cannot be blinded to allocation group.

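### At the planned 25% loss, the 5% rule makes multiple imputation the main analysis, but the plan gives practice no place in it; the standard errors would be modestly wrong even after the regression is repaired

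*Protocol article*

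**What the plan says.** The Protocol article allocates whole practices (Randomisation and blinding): "Each practice will be randomly assigned to either the intervention or control arm on a 1:1 basis". The Sample size section assumes an ICC of 0.05 and plans for drop-out: "Allowing for a 25% loss to follow-up, we would need to recruit 13 participants (i.e. patients) per cluster".

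The Data analyses section then sets these rules:

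- Model: "Between-group differences for all outcomes will be analysed using linear regression", with each outcome entered "as a dependent variable using the study group as an independent variable, adjusted for the baseline measurement of each outcome measure".
- Time points: "Each outcome variable will be analysed independently at T1 and at T2".
- Missing data: "If missing data for an outcome is > 5%, multiple imputation will be conducted".
- Software: "All analyses will be performed using IBM SPSS Statistics 26".

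The section mentions practice neither as a term in the regression nor as part of the imputation.

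**The concern.** The planned loss is five times the trigger, so the rule is not a contingency. If recruitment and retention go as planned, the main result for both primary outcomes comes from imputed data.

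In a practice-randomised trial, the way practice enters the imputation affects the standard error of the treatment effect:

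- If practice is left out, about a quarter of the outcomes are filled in without any practice effect. The variation between practices shrinks and the standard error is too small.
- If practice is entered as a fixed factor, sampling noise in 34 estimated practice means is added to the imputed values. The variation between practices is inflated and the standard error is too large.

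Both errors remain after a practice term is added to the final regression, so that repair alone is not enough. One choice gives extra false positives and the other lost power, and nothing in the stated rule decides between them.

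**Working it through.** **The plan's own figure.** Inputs from the Sample size section: difference 0.7, SD 1.8, two-sided 0.05, power 0.80, ICC 0.05, 10 patients per practice.

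- Per arm without clustering: 2 × (1.960 + 0.842)² × 1.8² / 0.7² = 103.8.
- Design effect: 1 + 9 × 0.05 = 1.45, and 103.8 × 1.45 = 150.5, against 15 × 10 = 150.
- 15 × 1.1 = 16.5, rounded up to 17 practices. 10 × 1.25 = 12.5, rounded up to 13 patients. 17 × 13 = 221 per arm and 442 in total.

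The stated total reproduces. With 25% lost, 13 × 0.75 = 9.75 patients per practice are observed and 3.25 are missing.

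**Assumptions not in the document.** Baseline–outcome correlation 0.5; T1–T2 correlation 0.7 (0.8 as a check); 20 imputations; ICC range 0.01 to 0.10; imputation at a single level.

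**Analytic check at ICC 0.05** (variance of the arm difference, residual SD set to 1):

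- Correct variance from observed data: 2/17 × (0.05 + 0.95/9.75) = 0.01735.
- *Practice left out.* Within-imputation: 2/17 × [0.75² × 0.05 + (9.75 × 0.95 + 3.25 × 1)/13²] = 0.01202. Between-imputation: 2/17 × 0.25² × (1/9.75 + 1/3.25) = 0.00302. Total: 0.01202 + 1.05 × 0.00302 = 0.01519. SE ratio √(0.01519/0.01735) = 0.94.
- *Practice as a fixed factor.* Between-imputation: 2/17 × 0.25² × 0.95 × (1/9.75 + 1/3.25) = 0.00287. Within-imputation: 0.01735 + 0.00287 = 0.02021 (before rounding). Total: 0.02021 + 1.05 × 0.00287 = 0.02322. SE ratio √(0.02322/0.01735) = 1.16.

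**Simulation** (2 × 17 practices × 13 patients, SD 1.8, about 25% missing at T2 depending on baseline, no true effect, final model with a random practice intercept, ICC 0.05, 3,000 trials):

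| Handling of missing outcomes | True SE | Reported SE | Ratio | Type I error |
|---|---|---|---|---|
| Observed data, no imputation | 0.208 | 0.205 | 0.985 | 5.4% |
| Imputed from arm + baseline | 0.209 | 0.193 | 0.92 | 6.4% |
| Imputed with practice as fixed factor | 0.210 | 0.240 | 1.14 | 2.5% |

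Repeat runs gave type I errors of about 6.0–6.6% with practice left out and 2.0–2.5% with practice fixed. Leaving practice out pulled the mean estimated ICC from 0.050 to 0.030. A separate simulation, with data missing completely at random and a test on practice means, gave ratios of 0.93, 1.16 and 1.00 for practice left out, practice fixed and no imputation.

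**Other ICCs, practice left out.** At 0.01 the ratio is 1.02 and type I error 3.9%. At 0.10 the ratio is 0.89 and type I error 6.9%; the practice-means simulation gave 0.88 and 7.4–8.9%.

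**Power at 0.7 points, practice as fixed factor** (SE overstated by 1.16, critical value 2.037 on 32 df):

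- If 1.8 is the unadjusted SD and the correlation is 0.5: SE = 1.8 × √(0.01735 × 0.75) = 0.205. Power goes from Φ(0.7/0.205 − 2.037) = 0.92 to Φ(0.7/0.205 − 2.037 × 1.16) = 0.85. Simulation gave 92% and 84%.
- If 1.8 is already the baseline-adjusted SD: SE = 1.8 × √0.01735 = 0.237. Power goes from 0.82 to 0.72.

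**Precision.** Imputing from arm and baseline gives a true SE of 0.209, against 0.208 without imputation, so nothing is gained. With T1 added, the true SE falls by about 1% when half of those missing T2 have T1, and by 2–4% when nearly all do (0.2043 against 0.2093; 0.1986 against 0.2072 at T1–T2 correlation 0.8).

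**For scale.** Linear regression without a practice term, as written, has type I error of about 11% with or without imputation.

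**The case against.** The article does not give an imputation model. Predictors and cluster handling are commonly left to an analysis plan, and the Study setting section says that a protocol is deposited in a public repository. A reader could say that the errors above belong to two poor models which the plan never chose. The effect is also small at ICC 0.05, absent at 0.01, and dwarfed by the missing practice term in the regression.

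Much of this stands, and it limits the point. Four stronger readings are tempting, and the document does not support them:

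- *The named software must give wrong standard errors.* The article names the software and says nothing about what its imputation can do. Single-level imputation is an assumption.
- *Imputation gains no precision.* This is true only with arm and baseline as predictors. The article does not rule out T1 as an auxiliary, which brings 1–4%.
- *Power falls below the planned 80%.* It does so only if 1.8 is already the adjusted SD, which the Sample size section does not say. Otherwise power stays at about 0.85.
- *Imputation is what makes the planned tests invalid.* As written, type I error is about 11% either way, because the regression has no practice term.

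The objection does not remove the rule itself. The article fixes a trigger that the planned loss exceeds, and its analysis section describes a patient-level analysis throughout. A team that repaired only the regression would still have miscalibrated intervals under either simple way of imputing.

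**Conclusion.** The point holds as a moderate one. At the planned 25% loss, multiple imputation becomes the main analysis of the follow-up outcomes, in a plan that mentions practice in neither the imputation nor the regression.

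Once the regression is corrected, the remaining error at ICC 0.05 is a standard error about 7–8% too small if practice is ignored, or about 14–16% too large if it is a fixed factor. The first is negligible at ICC 0.01 and brings type I error of about 7% or more at 0.10. In return, imputation adds little or no precision.

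These sizes rest on single-level imputation, a baseline correlation of 0.5 and loss close to 25%. The point ranks below the missing practice term in the regression, which is the larger defect.

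**What to change.** Replace the 5% rule. For each outcome, make the main analysis one linear mixed model on all observed T1 and T2 values, with arm, time, arm by time, the baseline value, correlated residuals within patient, a random intercept for practice and small-sample degrees of freedom. Report the T1 and T2 contrasts from it. The model is valid under the same missing-at-random assumption as imputation, uses T1 for patients lost at T2, and can be fitted in the named software. It also supplies the practice term that the regression lacks.

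If multiple imputation is kept, as a sensitivity analysis or otherwise, state that it is two-level with practice as a random effect, and name software that supports it.

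The cost is analysis wording only, with no new data. One small downside: predictors of drop-out must enter the model as covariates and cannot be used as auxiliary imputation variables.
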